## Discussion

4

Although studies have been made with the use of low-level laser therapy in TMD and on the effect of photobiomodulation on fatigue,^[13–16]^ this the first study to test this therapy in the prevention of fatigue in this region. The clinical relevance lies in the fact that longer dental procedures could take place if the patients are less prone to fatigue.

## Declarations

5

### Ethics committee

5.1

The Ethics Committee of University of Nove de Julho (UNINOVE) approved this project under process number 76402417.2.0000.5511, in accordance with the guidelines of the National Ethics Committee (CONEP). Any modifications to the protocol that may have an impact on the conduct of the study will be reported to the committee. An informed consent form (which was approved by the UNINOVE Ethics Committee) will be signed by the volunteers previous to their participation.

### Data collection methods

5.2

The authors were previously trained to collect data and perform the evaluations. All authors are qualified in laser therapy. The same researchers will enroll patients and assign them to interventions. All data will be entered electronically. The participants’ files will be stored in numerical order in a safe place and accessible only to the authors of this study.

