### Type of study

2.1

A randomized, blind, clinical trial will be conducted with both placebo and control groups. The guidelines for research involving human subjects stipulated in Resolution 466/2012 of the Brazilian National Board of Health will be followed and the study has been approved by the Human Research Ethics Committee of University Nove de Julho, under process number 76402417.2.0000.5511. The participants will sign a statement of informed consent after receiving clarifications regarding the objectives and procedures of the study.

The protocol is in accordance with the 2013 SPIRIT (Standard Protocol Items: Recommendations for Interventional Trials) Statement. The SPIRIT checklist can be found as an additional file and Figure 1 is the SPIRIT figure. SPIRIT was developed to provide guidance in the form of a checklist of recommended items to include in a clinical trial protocol, to help improve its content and quality.

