### Recruitment and randomization

2.4

Healthy male and female young adults enrolled at University Nove de Julho (Vergueiro campus) in São Paulo will be evaluated (Fig. 2). Since they will already be on campus, the process of recruitment will be simple. Patients will be divided by block randomization into the groups.

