### Induction of fatigue and EMG

3.1

The volunteer will be seated on a chair with back supported, eyes open, feet parallel on a rubber mat, and hands resting on thighs. The examination will be performed under 2 conditions: in normal postural position with mandible at rest; during maximum voluntary contraction (MVC) with Parafilm M placed between the teeth.

In the resting position, the volunteer will remain with the jaw relaxed, the teeth separated and the lips in contact for 15 seconds. For MVC, the volunteer will be instructed to place a Parafilm M between the maxillary and mandibular premolars and second molars bilaterally and perform isometric contraction for 45 seconds after a verbal command.

A contraction protocol will be used to induce fatigue.^[7]^ MVC clenching the teeth will be performed to record the time until initial exhaustion of the masseter muscle (determined by EMG). The groups will then be submitted to the interventions and MVC will be performed a second time to record the time until initial exhaustion of the masseter muscle (determined by EMG). During the procedures, the volunteers will receive verbal encouragement as well as visual feedback on the monitor to maintain MVC. Before the readings, the volunteers will undergo training of the procedure for the acquisition of the EMG signal.^[8]^

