### Research diagnostic criteria for TMD

3.3

The research diagnostic criteria for temporomandibular disorder (RDC-TMD) questionnaires will be filled out by the volunteers for the diagnostic investigation of TMD. A specific clinical examination will be performed always by the same previously trained evaluator and will consist of palpation of the trapezius, sternocleidomastoid, temporal, masseter, digastrics and medial pterygoid muscles, palpation of the TMJs, analysis of mandibular movements (vertical and horizontal movements measured with digital calipers), the verification of joint sounds and the investigation of frequent headaches, facial pain, fatigue and difficulty chewing, bruxism, psychologic aspects, and parafunctional habits. Volunteers classified in groups I, II, or III of the RDC-TMD will be excluded from the study.

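### Enrolment and assignment are in the same hands under block randomization, no masked tester is stated for an effort-dependent outcome, and the unqualified blind label is supported only for volunteers in laser versus sham

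*Protocol article*

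**What the plan says.** On allocation, section 2.4 (Recruitment and randomization) says "Patients will be divided by block randomization into the groups". Section 5.2 (Data collection methods) adds "The same researchers will enroll patients and assign them to interventions".

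On evaluation, section 5.2 says "The authors were previously trained to collect data and perform the evaluations" and "All authors are qualified in laser therapy". It does not name the person who delivers the laser.

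On blinding, section 2.1 (Type of study) says "A randomized, blind, clinical trial will be conducted with both placebo and control groups". No role is attached to the word blind. Section 3.2 (Laser application protocol) describes the sham: the device is off and recorded sounds are played to the volunteer. According to the abstract, the third group receives no intervention.

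On the outcome test, section 3.1 (Induction of fatigue and EMG) has one maximum voluntary contraction (MVC) before the intervention and one after it, each giving a time to initial exhaustion of the masseter determined by EMG. During these procedures "the volunteers will receive verbal encouragement as well as visual feedback on the monitor to maintain MVC".

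**The concern.** Three features combine.

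- **Allocation.** The people who decide whether and when a volunteer enters also assign the arm. With blocks, past assignments carry information about the next one. Unless the sequence is kept from them, entry can be influenced by the expected arm.
- **Testing.** Time to exhaustion depends on how hard and how long the volunteer clenches, and someone is urging the volunteer on. If that person knows the arm, encouragement can differ between arms without intent. Bite force is also effort-dependent. Palpation pain and passive opening depend on the pressure that the examiner applies.
- **Label.** A reader of section 2.1 would take the whole three-arm comparison as blind. The design cannot deliver that.

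At stake is the interpretation of any difference between arms. Bias from these sources enters when volunteers are allocated and tested, and the analysis in section 3.7 is not built to detect or correct it.

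**Working it through.** The article gives no figure on this point, so there is none to reproduce. The check has three parts.

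**1. Who can be blind, from the text**

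| Role | Laser v sham | Either v control |
|---|---|---|
| Volunteer | masked by the sham (section 3.2) | not masked; controls receive nothing |
| Whoever operates the device | not masked; it is off for sham | not masked |
| Person running the second MVC and other readings | not stated | not stated |

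Only one cell supports the word used in section 2.1.

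**2. Predictability of block allocation**

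Inputs from section 2.3: three arms, 26 each, 78 in total. The remaining inputs are assumptions: one fixed block length, known to the recruiter; all past assignments known; the next assignment not concealed.

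A fixed block holds *m* of each arm, so its length is *b* = 3*m*. To fill 26/26/26 with complete blocks, *m* must divide 26, so *m* = 1, 2, 13 or 26 and *b* = 3, 6, 39 or 78.

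*Share certain.* An assignment is certain when only one arm remains in the block. A given slot's assignment is of this kind if it comes after all 2*m* assignments to the other two arms, which has probability 1/(2*m* + 1). That is also the expected share of certain assignments.

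*Share guessed.* The best guess is the arm with most places left, right with probability (largest number left)/(total left), averaged over all block orders.

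- *b* = 3: (1/3 + 1/2 + 1)/3 = 0.611.
- *b* = 6: the expected values at positions 1 to 6 are 0.333, 0.400, 0.500, 0.533, 0.600 and 1.000; the sum is 3.367, and 3.367/6 = 0.561.
- *b* = 39 and 78: the same recursion by computer.

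| Block length | Certain | Guessed correctly |
|---|---|---|
| 3 | 1/3 = 33.3% | 61.1% |
| 6 | 1/5 = 20.0% | 56.1% |
| 39 | 1/27 = 3.7% | 44.4% |
| 78 | 1/53 = 1.9% | 41.4% |
| No knowledge | 0% | 33.3% |

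Lengths 9 and 12 do not divide 78 (78/9 = 8.67; 78/12 = 6.5). They would give 14.3% and 53.2%, and 11.1% and 51.2%, inside the same range.

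**3. Sensitivity of the result to unequal encouragement**

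Suppose there is no true effect, but encouragement shifts one arm by δ standard deviations. For 26 v 26, with a normal approximation and an assumed two-sided test at 0.05, the standard error of the difference is √(2/26) = 0.277 SD. The false-positive rate is 1 − Φ(1.96 − δ/0.277) + Φ(−1.96 − δ/0.277).

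| Assumed δ (SD) | False-positive rate |
|---|---|
| 0 | 5% |
| 0.1 | 6.5% |
| 0.2 | 11.1% |
| 0.3 | 19.1% |
| 0.4 | 30.3% |
| 0.5 | 43.8% |

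The documents give no SD and no basis for any value of δ. The table shows only how little unequal handling would be needed to matter.

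**The case against.** The strongest reply is that the article condenses a fuller protocol and refers to a SPIRIT checklist that is not shown. Block length, list generation and concealment may be set out there. One person can enrol a volunteer and then open the next sealed envelope, so section 5.2 is compatible with concealment. Block lengths may vary. The endpoint is determined by EMG, which limits reader judgement. Each person's change from a pre-intervention MVC is used, and the volunteers are healthy, free of TMD and aged 18 to 34, which leaves less prognostic variation to select on. Section 3.3 also shows some division of roles: "A specific clinical examination will be performed always by the same previously trained evaluator". A sham arm beside an untreated arm is a recognised design.

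Much of this stands, and it rules out several stronger readings that a reader might infer:

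- *That allocation is foreseeable.* This needs known block lengths and no concealment; the article states neither.
- *That the authors deliver the laser and give the encouragement.* Section 5.2 says only that they are qualified in laser therapy, and section 3.1 does not name who encourages.
- *That the bias must favour the laser arm.* Nothing in the text fixes its direction.
- *That the blind label is simply false.* Volunteer masking for laser versus sham is described.

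What the reply does not remove: the shared roles in section 5.2 are stated, not left unsaid. A single trained evaluator is not thereby a masked one. EMG fixes how the endpoint is read, not how hard the volunteer is urged to clench. No fuller document could blind an untreated volunteer or the person who switches the device off.

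**Conclusion.** The point holds as a risk created by a stated arrangement, together with a label wider than the design. Enrolment and assignment share the same hands under block randomization, the authors evaluate, and no separation or masking is stated for whoever runs the post-intervention maximum-effort test. Blind is supported only for volunteers in laser versus sham.

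The size is conditional. With fixed, known and unconcealed blocks, predictability lies between the figures for length 78 and length 3 in the first table. With proper concealment, that route to selection bias is closed. The false-positive rates rest on assumed shifts and are illustrations, not estimates. Neither calculation shows that bias will occur. The sample size is not affected.

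**What to change.** 1. **Section 5.2 and section 2.4.** Replace the shared-role statement. An existing author who neither enrols nor assesses generates and holds the sequence, with varying block sizes and sealed, numbered envelopes. Each envelope is opened only after all baseline readings, including the first MVC. If the full protocol already conceals allocation, state it here.
2. **Sections 3.1 and 3.4 to 3.6.** An existing author unaware of arm runs the second MVC, bite force, range of movement and palpation, with scripted encouragement. The tester should not be able to recognise controls by how or when they return; the investigators should say how this is arranged.
3. **Section 3.1.** Score time to exhaustion from coded EMG files by a fixed rule.
4. **Section 2.1.** Describe the trial as participant-blind for laser versus sham only, with a blinded assessor. Treat laser versus sham as the blinded comparison, and say that volunteers are not blind in comparisons with control.

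The cost is envelopes, a script, file coding and a rota. No change to the sample size is needed. That existing authors suffice is an assumption: the article speaks of several authors but their number is not visible, and the rota must keep the sequence holder apart from enrolment and testing, and the tester apart from treatment.

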### Discontinuing intervention

5.3

If volunteers become ill or do not adapt to therapy, it will not be possible to continue laser therapy. Interventions will be made while the participants are at the university, to make it easier for them to come, avoiding absences. No adverse effects are expected.

### Availability of data and materials

5.4

The data sets generated and analyzed during the present study are available from the corresponding author at reasonable request. After the analysis of the data, volunteers will be invited to a meeting and the results will be shared and they will become public.
